2. What is the effect of the key moderating factors hypothesised on the effective implementation of the model?	Putative moderating factors derived from theory (see Fig. 2), and from Theory of Change map^19^: Participant responsiveness/satisfaction Resources Recruitment/service uptake Model description and communication	See Table 3 Facility case study Cohort questionnaire Qualitative interviews Training logs (mhGAP) Activity logs (e.g. awareness raising)	Logistic regression Analysis to compare outcomes with and without moderating factor of interest Qualitative interviews to explore impact of moderating factors on outcomes
3. What are the contextual factors that promote or frustrate optimal service delivery, access and maximum coverage?	Contextual factors in local service and political environment	See Table 3 Situation analysis Facility case study	Qualitative interviews to understand perceived importance of contextual factors on implementation
4. How do patients use the service, and what is the level of accessibility and acceptability of the service for patients, carers and staff?	Accessibility Distance travelled Costs (direct and carer opportunity costs) Other barriers to access Acceptability Cultural understanding and adaptation Awareness-raising effectiveness Perception of patients and staff	Cohort questionnaire: PACIC Qualitative focus group Discussions with patients, carers and staff	Distance and cost form part of assessment of moderating factors (below) Comparison of PACIC scores across sites to assess service use satisfaction against intended programme attributes Qualitative interviews to assess both extent of accessibility and acceptability, and granular perceptions of the service

mhSUN, Mental Health Scale Up Nigeria; mhGAP, Mental Health Gap Action Programme; PACIC, Patient Assessment of Chronic Illness Care.

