A situation analysis carried out at the programme development stage.A facility case study comprising quarterly evaluation of facilities, including a facility checklist of human resource presence, medication availability and infrastructure, as well as record of changing context.Log books of intervention elements such as governance processes, advocacy meetings, awareness campaign, training and supervision.Routine health information system recording service use statistics, disaggregated by primary diagnosis and gender, and patient clinical records.Supervision record forms documenting monthly supervision visits, incorporating assessment of quality of care provided.Cohort of patients comprising a sample of patients with each of the three major diagnoses of epilepsy, psychosis and depression (the priority conditions for the service) will be interviewed on entry to the service and at 6 months. Data includes validated questionnaires on clinical, human rights and disability outcomes, patient satisfaction and service use (including costs). A conservative sample size of 200 participants per diagnosis has been calculated to achieve sufficient power to measure change in outcomes on clinical and disability measures. This was based on outcomes of similar studies exploring integration of treatment of depression, psychosis and epilepsy in primary care in LMIC settings.^42,43^Qualitative data collected through in-depth key informant interviews, and observation notes kept during site visits. Processes to engage and gain buy-in from relevant actors are built into the governance of mhSUN, so we expect to be able to obtain consent from key actors.

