### Coverage/reach

This refers to the proportion of the target group are affected by the intervention (see Supplementary File 3 for a process flow diagram). This is a key consideration for efficiency and equity, and is of great interest to decision makers in government – the target of our research results. Three levels of coverage will be measured.^46^ The first level is contact coverage. Routinely collected data available at the clinic will be used to measure clinic attendance for mental disorder. Published mental disorder prevalence data, weighted for the demographics of the local community, will then be used to obtain the denominator for calculation.

The second level is adequate coverage. To assess the proportion of the people receiving an adequate intervention, the cohort questionnaire included a measure of patient satisfaction with service (Patient Assessment of Chronic Illness Care (PACIC) questionnaire^47^). We will compare the PACIC results with the supervision report, which scores patient treatment on a scale based on whether assessment, diagnosis, treatment and appropriate referral were carried out by attending clinicians (general Primary Health Care nurses). Although specific tools to assess quality of clinical care in Primary Health Care in LMICs have been developed (e.g. the ENhancing Assessment of Common Therapeutic factors tool^48^), this is prone to the Hawthorne effect. We have tried to avoid this by assessing anonymous patient notes for quality of clinical care.

The third level is effective coverage. This is defined as the proportion of patients achieving recovery based on 6-month clinical (symptom reduction) and disability outcome data (WHO Disability Assessment Schedule 2.0, which has been used extensively in similar studies of mental healthcare reform,^49,50^ including in Nigeria^51^). For depression, we used the Patient Health Questionnaire-9, which has been validated and used widely in Nigeria;^52^ for epilepsy, we used a count of seizures in the previous month. Clinical Global Impression–Severity score was used for all participants entering the cohort study, and this was used as a proxy for psychosis, where a good correlation has been reported for more complex change measures.^53^ In addition, quality of training is assessed with standard mhGAP pre-and post-questionnaires, and competency forms part of supervision reports.

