a. See supplementary material for facility case study and cohort questionnaire details.

PACIC, Patient Assessment of Chronic Illness Care; CSRI, Client Service Receipt Inventory; HES Nigeria, Household Expenditure Survey; HMIS, (routine) health management information system at Primary Health Care.

We will use descriptive analysis of facility-level data and logs (training attendance, medication availability, staff presence, etc.), using data at different time periods to compare outcome with and without the relevant moderating factors of impact of awareness-raising programme on service uptake; availability (or not) of medication, and any correlation with service provision and uptake; and actual rate of programme components bedding down (compared with initial plans and expectations).

In addition, as the programme is being carried out in two states (and within seven and eight districts within each of these), we will be able to examine the effect of differences in implementation across location; for example, the impact of localised policies on drug distribution on availability, the effects of support from local political and health leadership, and the influence of insecurity on implementation in different districts.

For data collected through the cohort questionnaire, we will be able to summarise data on costs, service use and other cross-sectional information, and carry out logistic regression analyses (using Stata for Windows version 9 to generate odds ratios) to identify associations between different factors and outcomes, such as looking at whether a group reporting easy versus barriers to access to a clinic had better outcomes.^55^ Although such analysis risks being underpowered, we will explore whether the results confirm or refute our hypotheses, and we will be triangulating this with the qualitative work, allowing us to explore potential mechanisms, using the experience and expertise of key informants.

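### The cohort moderator analysis names only logistic regression, so 6-month scores and counts must be cut into categories, at a loss of power in an analysis the plan says may be underpowered

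*Protocol article*

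**What the plan says.** Under Moderators, the protocol article says that for the cohort questionnaire it will "carry out logistic regression analyses (using Stata for Windows version 9 to generate odds ratios) to identify associations between different factors and outcomes". It gives one illustration: "such as looking at whether a group reporting easy versus barriers to access to a clinic had better outcomes". It then says: "Although such analysis risks being underpowered, we will explore whether the results confirm or refute our hypotheses". Table 1 (research question 2) also lists logistic regression, followed by "Analysis to compare outcomes with and without moderating factor of interest".

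Under Coverage/reach, the outcome measures are WHODAS 2.0, PHQ-9 for depression, a monthly seizure count for epilepsy, and CGI-Severity for all cohort participants (standing in for a psychosis measure). The same section defines effective coverage as "the proportion of patients achieving recovery based on 6-month clinical (symptom reduction) and disability outcome data", which is a yes/no outcome. No threshold is given.

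Under Methods, data sources and analysis, patients are interviewed on entry and at 6 months, and the sample size statement reads, in part: "A conservative sample size of 200 participants per diagnosis has been calculated to achieve sufficient power to measure change in outcomes on clinical and disability". Table 3 takes four cohort moderators from the questionnaire: PACIC, cost, socioeconomic status from household expenditure, and distance.

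**The concern.** An odds ratio from logistic regression needs a categorical outcome. The cohort supplies scores and a count, measured at entry and again at 6 months. Cutting them discards the differences among patients on the same side of the threshold. The article presents the low power as a risk to be met by triangulation with interviews, but part of it comes from the model chosen and can be recovered without more patients.

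Research question 2 asks what effect the hypothesised moderators have, and the results are to be read as confirming or refuting hypotheses. If power is low, an odds ratio near 1 refutes nothing, and a real moderator may be set aside or judged on interview data alone.

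**Working it through.** **Inputs from the article.** 200 patients in each of three diagnoses, so 600 in all; logistic regression with odds ratios; score and count outcomes at entry and 6 months; one two-group example of a moderator.

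**Assumed, because the article gives no figure.** Two-sided 5% level; normally distributed score and moderator; 40% recovered; moderator split at its median where split; entry-to-6-month correlation 0.5; association 0.15 SD of outcome per SD of moderator; no clustering; no dropout unless stated.

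**1. The plan's own figure.** The 200 cannot be reproduced, since no effect size, SD, level or power is stated. Worked backwards for a paired change, d = (z for the level + z for power)/√n:
- 80% power: (1.960 + 0.842)/√200 = 0.198.
- 90% power: (1.960 + 1.282)/√200 = 0.229.

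So 200 is adequate for a modest within-patient change. It was not derived for the moderator regression.

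**2. Information kept after a cut.** For a normal variable cut so that a share p falls on one side, relative efficiency is φ(c)²/[p(1−p)]. For a weak association, the efficiencies of two cuts multiply.
- Outcome cut at 40%: 0.3863²/0.24 = 0.622, a loss of 38%.
- Moderator cut at the median: 0.3989²/0.25 = 0.637.
- Both cut: 0.622 × 0.637 = 0.396, a loss of 60%.
- Both cut and the entry score left out: 0.396 × (1 − 0.5²) = 0.297.

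Of 200 patients, these leave the equivalent of 200 × 0.622 = 124, 200 × 0.396 = 79 and 200 × 0.297 = 59.

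Range: cutting the outcome alone keeps 0.637 at 50/50, 0.576 at 30/70 and 0.490 at 20/80. Cutting both keeps 0.405 at the medians and 0.240 at 20/80 on each side.

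**3. Power by simulation** (independent runs agree to within about 3 points):

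| Analysis | n=200 | n=600 |
|---|---|---|
| Linear, continuous moderator, entry score | 69% | 99% |
| Logistic, continuous moderator, entry score | 45% | 89% |
| Logistic, moderator split, no entry score | 27% | 63% |

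The second row is the like-for-like cost of the named model. The third adds two choices that the article does not fix. With 20% loss to follow-up, the three rows are about 59%, 36% and 21–24% at n=160, and about 96–97%, 80% and 52–55% at n=480.

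**4. Cross-check by another route.** Take the correlation that a continuous analysis of 200 detects with 80% power, r = 0.197. Splitting only the outcome at its median lowers power to about 62%; splitting both lowers it to about 43%. Matching the continuous analysis after both splits would take 1/0.405 = 2.47 times the sample, about 493 in place of 200.

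**The case against.** The strongest reply is that logistic regression fits an outcome the article defines. Recovery at 6 months is a yes/no coverage measure, and it puts depression, epilepsy and psychosis on a common footing despite their different clinical scales. That stands: the logistic model is coherent for recovery and should be kept. What it does not answer is why no model of the scores is named when the scores are collected twice.

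Three stronger readings are tempting but not supported:
- **That the regression is run within each diagnosis.** The Moderators section does not say so. The per-diagnosis figure belongs to the sample size for change, and a pooled logistic model is compatible with the text.
- **That every graded moderator will be split in two.** The easy-versus-barriers comparison is a single illustration. Logistic regression accepts continuous covariates, and the questionnaire is in supplementary material not shown, so the access item may itself be categorical. The wording in Table 1 about comparing with and without a factor is used under Moderators for the descriptive analysis of facility data and logs, where presence or absence is natural.
- **That over half the information is lost as planned.** That holds only if both sides are split. The named model on its own forces only the outcome cut.

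It is also fair that the article claims only a risk of low power, treats the analysis as exploratory and plans triangulation as part of a mixed-methods design. That limits the consequence. Cut-points and covariates may properly sit in a fuller plan; the choice of model, however, is stated here.

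**Conclusion.** The point holds in a limited form. The article names one inferential model for the cohort moderators, and that model requires scores and counts to be reduced to categories. Under the stated assumptions this alone costs about 38% of the information, or 24 points of power at n=200 (45% against 69%) and 10 points at n=600 (89% against 99%). If the worked example's two-group coding were also applied and the entry score left out, power would be about 27% and 63%.

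The recovery rate, the correlation, the effect size and normality are all assumed. Clustering is ignored, although patients come from two states with seven and eight districts; allowing for it would lower the power figures, pooled ones included. The direction of the comparison does not depend on whether the models are run by diagnosis.

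**What to change.** Keep the logistic model for recovery. Add beside it:
- A linear model of 6-month WHODAS 2.0 score on each moderator, adjusted for entry WHODAS, diagnosis and state, pooled over the three diagnoses, with a moderator-by-diagnosis check and standard errors that allow for clustering by facility or district.
- In depression, the same model for PHQ-9 adjusted for entry PHQ-9.
- In epilepsy, a count model for seizures.
- Distance, cost, expenditure and PACIC as continuous terms wherever they are recorded that way, in the logistic model too.

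The cost is analysis wording and no new data. The drawbacks are a second set of estimates, in scale points rather than odds of recovery, and a pooled estimate that relies on the interaction check.

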### Research question 4: accessibility and acceptability

Ensuring accessibility and acceptability was a consideration throughout the design of the intervention, as demonstrated by the use of ToC and extensive engagement with local authorities. Language and cultural understanding are a consideration throughout in the research and programme elements, as shown by awareness-raising and local concepts of mental illness being incorporated into communication materials. Accessibility and acceptability will be assessed through the cohort questionnaire (PACIC), and in qualitative interviews with patients, carers and healthcare staff, drawing on similar research.^56^ Focus group discussions will be used both in qualitative evaluation of acceptability of the intervention, and in triangulating with factors deemed to influence outcomes, as acceptability is a potential moderator (part of Participant Responsiveness (see Fig. 1).

### Strengths and limitations of the study design

The study is a pre-planned process evaluation exploring local contextual factors, filling a gap in literature for mental health integration into primary care that is mainly of outcome evaluations to date. There is a strong theoretical basis for the intervention, based on international guidelines (WHO mhGAP) that are widely accepted normative standards. Local experience and context are considered with a ToC approach. The use of mixed methods, with data capture through routinely collected key data and through purposive quantitative and qualitative methods, allows triangulation of results from different sources, testing assumptions from the ToC and allowing reflection by key actors of potential mechanisms. Weaknesses in routine data collection will be managed with provision of additional statistics forms for mental health and related processes.

A key limitation is the many external factors that are likely to influence the implementation of the mental health intervention in a generally weak and fragile system, and a context of political uncertainty with a history of communal violence. However, the research aims to inform practice in just these settings and a real-world evaluation is of more value than a highly controlled experimental design. These factors will be captured and their impact interpreted through the study design used.

### Ethics and dissemination

Ethical approval has been given by the ethical review boards of London School of Hygiene and Tropical Medicine (Ref: 11056 /RR/5812), Ibadan University and the two Federal Neuropsychiatric Hospitals in Calabar and Kaduna. Consent will be obtained from all participants interviewed in the quantitative or qualitative components of the research. Extensive engagement was carried out with the local primary care services, including gaining permission from the State Ministries of Health (Commissioner, Primary Care Director), during programme design. At the local government area level, programme staff visited the local government Chairman and discussed the research with the Supervisory Councillor for Health, and each Primary Health Care unit head and relevant local government area monitoring and evaluation leads. A Memorandum of Understanding was signed with each state Ministry of Health and local government area, which gave formal authority for the work. In addition to these local health officials, local traditional leaders, tradition healers and religious leaders were regularly visited throughout the period of the study.

In Kaduna, most data will be collected in Hausa, and surveys questionnaires have been translated and back-translated accordingly. In both sites, research assistants speak the range of local languages. Interviews will be transcribed and de-identified. The number of key informants will be relatively low, but we still do not expect it to be possible to identify individuals. Recognising language and literacy issues, clear participant information sheets have been developed, and research assistants have been taught to share relevant information clearly (verbally) and to respond to queries. Data will be securely stored throughout the process, including through the use of mobile digital data collection, and is only accessible to the research team members who possess a password (primary investigators and research coordinators at sites). All data for the cohort is anonymised at the point of collection. Other data collected at the sites will be stored by the research coordinator in a locked office, and on a password-protected computer. It will be sent at regular intervals to a server established for this purpose at London School of Hygiene and Tropical Medicine.

Safety of research and implementation teams is a major consideration in this project because there is a history of communal violence in both states. Local districts were chosen to avoid this as much as possible, but it is felt important to carry out research in these settings that represent a large proportion of Africa, where mental healthcare is most needed and least available. Procedures will be put in place to minimise risk, guided by site teams and based on local knowledge of the risks at any particular time. This process (used during the research phase) will reflect real decision-making processes used in implementing programmes in practice.

As with other mental health service reform programmes at a pilot scale, the study's aim of influencing service planners is the main justification for a process evaluation study. The study aims to directly inform the investment and policy decisions of political and health leaders, and the Federal Ministry and State Ministries of Health in Nigeria are the primary target for dissemination, but results would be of interest to other governmental and civil society implementers, particularly in wider sub-Saharan Africa and in LMICs more broadly.

Resources have been allocated to share results with the National Mental Health Action Committee of the Federal Ministry of Health and in meetings at state Ministries of Health, as well as directly with those involved in the study in community meetings.

We plan to publish the results of this work in two separate papers (in addition to the development paper already published): research questions 1–3, where analysis will draw together fidelity and outcomes with moderators and contextual factors; and a separate paper on accessibility and acceptability of the intervention.

In addition to peer-reviewed academic literature, we will use networks of global mental health, such as the Mental Health Innovation Network (www.mhinnovation.net), which is widely accessed by implementers and policy makers. We expect to be able to provide the mhSUN programme implementers with learning that they may apply to refinement of the model to facilitate improved outcomes and sustainability, and will hold feedback sessions to local implementers and relevant stakeholders. In this way, we hope that the results of the work will be of value both locally and more broadly.

## Data Availability

As a protocol paper, data availability is not applicable to this article because no new data were created or analysed in this study. However, any information related to the study protocol are available on request from the corresponding author, [name]
